## Discussion

Mesenchymal stem cells have a strong potential for self-renewal and differentiation to multilineage cells. They can secrete several extracellular matrix molecules, growth factors, and cytokines that play a pivotal role in the regulation of angiogenesis and immune and inflammatory responses [19, 43]. Currently, several clinical trials have found potential value in using MSCs in healing chronic and acute wounds and scar remodeling [44].

To assess the efficacy and feasibility of autologous bone marrow-derived MSCs in the treatment of chronic nonhealing ulcers, researchers designed a randomized control study on a series of 24 participants with a history of nonhealing leg ulcer [33]. After 12 weeks, compared with control participants, the treatment participants had significant improvement in reduction in ulcer size. These results indicated that autologous implantation of bone marrow-derived MSCs in nonhealing ulcers accelerated the healing process. A single-arm clinical trial also indicated that autologous MSCs were shown to be therapeutically effective in patients with skin wounds [32]. To identify better cells for the treatment of diabetic foot ulcers, a randomized controlled trial was conducted on a sample of 41 type 2 diabetic patients with bilateral foot ulcer [45]. All patients were injected intramuscularly with bone marrow MSCs, bone marrow-derived mononuclear cells, or normal saline as placebo. They found that bone marrow mesenchymal stem cell therapy might be more effective than bone marrow-derived mononuclear cell therapy in promoting foot ulcer healing in diabetic patients. Another similar randomized controlled trial also obtained a similar result [46]. The frequency of major limb amputation was lower in a group treated with autologous bone marrow stem cells than in a group receiving standard medical care. Meanwhile, a meta-analysis demonstrated that autologous stem cell transplantation can be considered a safe and effective approach for treatment of many patients with diabetes mellitus [47].

Although previous results of trials with MSCs in wound healing have been reported, the application of MSCs on Cesarean section skin scars has not yet been investigated. In this prospective, randomized, double-blind, placebo-controlled study, we aim to investigate the possible effects of MSCs in women’s skin scars after Cesarean delivery. We hypothesize that MSCs can enhance wound healing, reduce hypertrophic skin scars, and decrease wound infection. To our knowledge, this trial is the first to investigate the potential of the therapeutic use of MSCs for the management of women’s skin scars after Cesarean delivery. The outcomes from this trial will help to determine the efficacy and safety of MSC treatment in Cesarean section skin scars. The results will also identify a therapeutically effective dose of MSCs in preventing hypertrophic scars and wound infections risk factors. It will give us an effective therapeutic strategy to combat Cesarean section skin scars, even with uterine scarring.

A limitation of this trial is that this is a single-center clinical trial, which will limit the extrapolation of results. Meanwhile, loss of participants at follow-up is possible, especially for nonresponders in the prospective trial study. Notwithstanding its limitations, this trial will suggest whether MSC can be a safe and effective in the treatment of Cesarean section skin scars.

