## Background

Over the past decades, Cesarean delivery has already become a very common method of delivery around the world, especially in low-income countries [1]. In China, although the Cesarean rate has decreased in individual megacities, the overall annual rate has still increased, reaching 34.9% in 2014, from 28.8% in 2008 [2]. Hypertrophic scars and wound infections have affected younger mothers and frustrated obstetricians for a long time. As one of the top three hospital-acquired infections, wound infections can prolong hospitalization and greatly increase the rates of hospital readmission, risk of death, and overall costs of healthcare [3]. It is reported that the incidence of wound infections ranges from 3% to 20% in women after Cesarean delivery [4]. In addition, hypertrophic scars and psychological stress are causes of dissatisfaction in women after Cesarean delivery.

The cutaneous wound healing process is very complex. It requires a variety of cells to collaborate, such as resident cells of the skin, hematopoietic cells, and immune cells [5]. Many complex factors, such as abnormal macrophage polarization, abnormal keratinocyte and fibroblast migration, proliferation, differentiation and apoptosis, impaired recruitment of mesenchymal stem cells (MSCs) and endothelial progenitor cells, and decreased vascularization may contribute to an abnormal wound healing process [6–8]. It is also reported that enhanced and prolonged expression of tumor necrosis factor-alpha contributes to abnormal wound healing processes [9, 10].

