### Interventions

Eligible participants, who have signed informed consent forms, will be randomized to placebo, low-dose (3 × 10^6^ cells) or high-dose (6 × 10^6^ cells) groups, receiving transdermal hydrogel MSCs or placebo once a day for six consecutive days. Each pump dispenses 1.0 ml gel (including 1 × 10^6^ cells or none). The justification of doses is based on previous studies for other indications [35, 36] and our preliminary experiment (unpublished). Each pump, either MSCs or placebo, has the same external characteristics except for a digital tag, to allow blinding of the intervention. After suturing the skin incision as usual, the first intervention will take place on the operating table and the remaining five interventions will take place in the postnatal ward. Participants in the placebo group will receive placebo hydrogel once a day for 6 days; those in the low-dose group will receive one dose of hydrogel with cells once a day for three consecutive days and then placebo hydrogel for the next three consecutive days; those in the high-dose group will receive cells for 6 days.

The government has been committed to promoting cooperation between governments, academia, pharmaceutical companies, biotechnology firms, and private investors to research and evaluate MSC therapies, since they are advanced therapies [37, 38]. The Health-Biotech Pharmaceutical Company (Beijing, China) manufactures both MSCs and the placebo hydrogel. The products will be provided without charge. The MSCs are extracted from the umbilical cord, which is donated by a healthy donor who has provided informed consent. Detailed descriptions of the method have been given in a previous article [39].

The study duration will last for 6 months, including a 1 week run-in period and 6 months of follow-up. All participants will be assessed at 0.5, 1, 3, and 6 months during the follow-up period. Table 2 provides the time points and specific measurements of data. Cosmetic use may affect wound function. If participants use cosmetics in the follow-up period, they will be withdrawn from the study.

**Table 2 Tab2:** Schedule of visits and assessments

Time point (weeks)	2	4	12	24
Vancouver Scar Scale		√	√	√
REEDA scale	√			
Erythema		√	√	√
Pigmentation		√	√	√
Scar thickness		√	√	√
Scar area		√	√	√
Immunoglobulin		√	√	√
Satisfaction		√	√	√
Adverse events	√	√	√	√

REEDA, Redness, Edema, Ecchymosis, Discharge, Approximation

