### Statistical analysis

All analyses will be conducted on the intention-to-treat and per-protocol principles. Regardless of whether participants received the randomized treatment, the intention-to-treat principle considers all of them as randomized. A complete case analysis will be performed if missing data for the randomized participants accounts for less than 5% of total data. Multiple imputations will be used if missing data is more than 5%. Dropouts will be included in the analysis by multiple imputations for missing data. The effect that the per-protocol participants and missing data might have on results will be assessed via sensitivity analysis. Subgroup analysis will be performed based on age and gestational age.

The primary comparison, both doses vs. placebo, will be analyzed using a superiority analysis. We will use the *t* test for the continuous outcome. Meanwhile, high dose vs. placebo and low dose vs. placebo will also be analyzed using the *t* test. Other outcomes will be analyzed using noninferiority analysis. The mean (and standard deviation) will be expressed for continuous variables, and numbers (percentages) will be expressed for categorical variables. Group variances will be compared using Leven’s test at the 0.05 significance level. Analysis of variance (ANOVA) will be used to analyze continuous data, and the *chi*-square test or Fisher’s exact test will be used for categorical data. To investigate the effects of treatment and time course, repeated measures ANOVA will be applied to determine changes in the continuous outcome data at each visit. R 3.1 software will be used for analysis.

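### The flat promise to identify an effective dose against hypertrophic scars and wound infections exceeds the design: total cells and days of cells rise together, no direct high-versus-low contrast is named, and a dose-specific infection effect is unlikely to be shown over most of the stated incidence range

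*Protocol article*

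**What the plan says.** - **Promise (Discussion).** "The results will also identify a therapeutically effective dose of MSCs in preventing hypertrophic scars and wound infections risk factors". The next sentence reads: "It will give us an effective therapeutic strategy to combat Cesarean section skin scars, even with uterine scarring". The Discussion part of the abstract makes the same uterine claim.
- **Arms (Interventions).** Participants "will be randomized to placebo, low-dose (3 × 10^6^ cells) or high-dose (6 × 10^6^ cells) groups". On pump content: "Each pump dispenses 1.0 ml gel (including 1 × 10^6^ cells or none"). On the regimens, "those in the low-dose group will receive one dose of hydrogel with cells once a day for three consecutive days and then placebo hydrogel" for three more days, while the high-dose arm receives cells on all six days.
- **Contrasts (Statistical analysis).** The primary comparison is both doses pooled against placebo, as superiority. In addition, "high dose vs. placebo and low dose vs. placebo will also be analyzed using the" *t* test. ANOVA is planned for continuous data and chi-square or Fisher's exact test for categorical data. Outcomes other than the primary are placed under noninferiority.
- **Infections.** The Background states that "the incidence of wound infections ranges from 3% to 20% in women after Cesarean delivery". Infections and hypertrophic scars are counted over six months as secondary outcomes.
- **Sample size.** 90 women, 30 per arm, derived from VSS alone (SD 1.68, difference 1.5, two-sided 0.05, power 0.90).

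**The concern.** The promise needs three things that the plan does not provide.

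1. To attribute a result to dose, amount and duration must be separable. Here the arm with more cells is also the arm with more days of cells.
2. To say that one active arm works better than the other, the two must be compared directly. If one arm reaches significance against placebo and the other does not, that is not evidence that the two differ.
3. To name a dose that prevents infection, enough infections are needed for a per-dose comparison to detect an effect.

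At stake is the conclusion of the trial. It could report an effective dose from two placebo p-values that fall on different sides of 0.05, and attach an infection claim that the counts are too sparse to carry. The uterine phrase has no outcome behind it at all.

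**Working it through.** **1. What separates the active arms.** Interventions gives 1 × 10^6 cells per pump.

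- Low: 3 cell days × 1 × 10^6 = 3 × 10^6, which matches the arm label.
- High: 6 cell days × 1 × 10^6 = 6 × 10^6, which matches the arm label.

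The labels thus agree with cumulative totals at one pump a day. The article does not state a daily amount for the high-dose arm; this is inferred from pump content and label. On this reading, doubling total cells and doubling days of cells are the same contrast, and no analysis can separate them. However, the abstract and the opening sentence of Interventions can also be read as 3 or 6 × 10^6 cells each day for six days. That reading conflicts with the regimen text later in the same paragraph.

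**2. Contrasts named.** Pooled vs placebo, high vs placebo and low vs placebo are named; high vs low is not. The three-group ANOVA is an omnibus test and gives no high-versus-low estimate.

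**3. What a direct contrast on VSS would give.** Inputs: SD 1.68, 30 per arm, no dropout.

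- Standard error = 1.68 × √(2/30) = 0.434.
- 95% CI half-width = t(0.975, 58) × 0.434 = 2.002 × 0.434 = 0.87 points.

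A hypothetical example shows why it is needed. Suppose high beats placebo by 1.0 point and low beats it by 0.7.

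| Contrast | Difference | t = difference / 0.434 | Two-sided p or CI |
|---|---|---|---|
| High vs placebo | 1.0 | 2.31 | p = 0.025 |
| Low vs placebo | 0.7 | 1.61 | p = 0.11 |
| High vs low | 0.3 | 0.69 | 95% CI −0.57 to 1.17 |

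The two placebo tests suggest that only the high dose works, while the direct contrast shows no clear difference between the arms.

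**4. Wound infection, one dose arm vs placebo.** The article gives no infection power figure to reproduce. Inputs: 30 per arm, incidence 3% to 20% from the Background, two-sided Fisher test at an unadjusted 0.05, no dropout. A superiority test is assumed, because the promise is one of prevention.

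- Expected placebo infections: 30 × 0.03 = 0.9 up to 30 × 0.20 = 6.
- With none in the dose arm, 5/30 vs 0/30 gives p = 0.052 and 6/30 vs 0/30 gives p = 0.024. At least 6 placebo infections are therefore needed.
- Power under complete prevention is P(X ≥ 6) with X ~ Binomial(30, p). Power under halving is the sum, over all pairs of counts with Fisher p < 0.05, of the product of the two binomial probabilities.

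| Placebo incidence | Power, every infection prevented | Power, rate halved |
|---|---|---|
| 3% | 0.02% | 0.02% |
| 10% | 7% | 2% |
| 20% | 57% | 10% |

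The uncorrected chi-square test needs only 4 placebo infections against none (p = 0.038). Under complete prevention its power is 1%, 35% and 88% at the same rates, although expected counts are then small.

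**5. Pooled 60 vs 30.** 3/30 vs 0/60 gives Fisher p = 0.035, while 2/30 vs 0/60 gives 0.109. Under complete prevention, P(X ≥ 3) is 6% at 3%, 59% at 10% and 96% at 20%.

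**6. Uterine scarring.** The outcomes listed are VSS, REEDA, erythema, pigmentation, scar thickness and area, milk immunoglobulins and complements, satisfaction, hypertrophic scar and infection counts, and safety. The gel is applied after skin closure, and no outcome is described as uterine.

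**The case against.** The strongest reply is that an effective dose can mean one that beats placebo. The plan tests each dose against placebo, and nowhere says that it will rank the doses by comparing p-values. The primary aim speaks of the three groups, ANOVA is planned, and follow-up contrasts may sit in a fuller document. Defining dose as total cells is a disclosed choice, and neighbouring sentences in the Discussion are more cautious.

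Much of this stands, and it rules out several stronger readings that a reader might infer:

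- *A per-dose infection effect could never be shown.* Not supported: at 20% incidence with complete prevention, Fisher power is 57%.
- *The plan ignores the individual doses or the three-group comparison.* Not supported: both are planned, and only a direct high-versus-low contrast is absent.
- *The arms differ only in course length.* Not supported: they also differ in total cells, and the point is that the two rise together.
- *No infection conclusion of any kind is possible.* Not supported: the pooled comparison does better, though only under the optimistic assumption of complete prevention.
- *The trial will draw uterine conclusions.* No planned analysis could produce one. The fault is in the wording.

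What the reply does not meet is the unqualified promise itself. The article lists its pairwise contrasts and leaves out the one between the active arms. The limitations mention only the single center and loss to follow-up.

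**Conclusion.** The concern holds as a mismatch between stated claims and design. On the regimen text, total cells and duration are fully confounded. A difference between active arms could be inferred only from unequal placebo p-values or an omnibus ANOVA. A dose-specific infection effect is unlikely to be shown over most of the 3% to 20% range: Fisher power is 0.02%, 7% and 57% at 3%, 10% and 20% under complete prevention, and at most about 10% if the rate is halved. The uterine claim has no supporting outcome.

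These figures assume 30 evaluable women per arm, an unadjusted two-sided 0.05 and, for VSS, the planning SD of 1.68. Dropout would widen the VSS interval. For hypertrophic scars the documents give no event rate, so no power is claimed. The planned VSS comparisons with placebo are not invalidated by any of this.

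**What to change.** 1. Add high versus low on month-6 VSS, reported as a difference with a 95% CI. Base any statement that one active arm is better on that contrast.
2. In the Discussion, replace the promise to identify an effective dose with a statement that each active arm is compared with placebo and with the other. Note that total cells and duration of cell treatment cannot be separated.
3. Report infections by arm with confidence intervals and draw no dose-specific infection conclusion. Keep the pooled comparison as exploratory.
4. Delete the reference to uterine scarring from the abstract and the Discussion.
5. Reconcile the abstract and the opening of Interventions, which can be read as the labelled amount every day for six days, with the later regimen text and pump content. Which description is right is for the investigators to state.

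The cost is one extra contrast on data already collected, some rewording, and more modest claims.

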## Trial status

Participant recruitment is currently in progress. The first participant was recruited on 14 September 2016. We hope to complete enrolment for the trial by March 2018 with all 6 month follow-up data expected by September 2018.

## Abbreviations

ANOVA: Analysis of variance
MSCs: Mesenchymal stem cells
REEDA: Redness, Edema, Ecchymosis, Discharge, and Approximation
VSS: Vancouver Scar Scale
